## Abstract

**Background:**

Vector control tools have contributed significantly to a reduction in malaria burden since 2000, primarily through insecticidal-treated bed nets (ITNs) and indoor residual spraying. In the face of increasing insecticide resistance in key malaria vector species, global progress in malaria control has stalled. Innovative tools, such as dual active ingredient (dual-AI) ITNs that are effective at killing insecticide-resistant mosquitoes have recently been introduced. However, large-scale uptake has been slow for several reasons, including higher costs and limited evidence on their incremental effectiveness and cost-effectiveness. The present report describes the design of several observational studies aimed to determine the effectiveness and cost-effectiveness of dual-AI ITNs, compared to standard pyrethroid-only ITNs, at reducing malaria transmission across a variety of transmission settings.

**Methods:**

Observational pilot studies are ongoing in Burkina Faso, Mozambique, Nigeria, and Rwanda, leveraging dual-AI ITN rollouts nested within the 2019 and 2020 mass distribution campaigns in each country. Enhanced surveillance occurring in select study districts include annual cross-sectional surveys during peak transmission seasons, monthly entomological surveillance, passive case detection using routine health facility surveillance systems, and studies on human behaviour and ITN use patterns. Data will compare changes in malaria transmission and disease burden in districts receiving dual-AI ITNs to similar districts receiving standard pyrethroid-only ITNs over three years. The costs of net distribution will be calculated using the provider perspective including financial and economic costs, and a cost-effectiveness analysis will assess incremental cost-effectiveness ratios for Interceptor® G2, Royal Guard®, and piperonyl butoxide ITNs in comparison to standard pyrethroid-only ITNs, based on incidence rate ratios calculated from routine data.

**Conclusions:**

Evidence of the effectiveness and cost-effectiveness of the dual-AI ITNs from these pilot studies will complement evidence from two contemporary cluster randomized control trials, one in Benin and one in Tanzania, to provide key information to malaria control programmes, policymakers, and donors to help guide decision-making and planning for local malaria control and elimination strategies. Understanding the breadth of contexts where these dual-AI ITNs are most effective and collecting robust information on factors influencing comparative effectiveness could improve uptake and availability and help maximize their impact.

**Supplementary Information:**

The online version contains supplementary material available at 10.1186/s12936-021-04026-0.

## Background

The World Health Organization (WHO) estimated that in 2019, 229 million cases of malaria occurred globally, resulting in 409,000 deaths [1]. While this is a remarkable improvement in since 2000, the global downward trend in annual malaria incidence began to plateau in 2014 and, more recently, the COVID-19 pandemic has complicated future projections. Challenges in keeping hard-won gains, and in accelerating progress toward elimination, have led the WHO to describe the global fight against malaria as at a crossroads, calling for increased funding and to develop, optimize, and implement urgently needed new tools and approaches [2].

Attaining optimal coverage of populations at risk of malaria with vector control interventions—primarily insecticide-treated bed nets (ITNs) and indoor residual spraying (IRS)—remains a priority because of its importance in malaria control and elimination [3, 4]. Per WHO, optimal coverage refers to (1) providing populations at risk of malaria with access to ITNs coupled with health promotion to maximize use and (2) ensuring timely replacement; or providing these populations with the regular application of IRS. Either intervention should be deployed at a level that provides the best value for money while reflecting programmatic realities [5]. Unfortunately, the continued effectiveness of these interventions is threatened by the spread of pyrethroid resistance in most endemic countries [1], posing a significant risk to the sustained impact of these tools [2, 3]. Evidence shows that standard pyrethroid-only ITNs (which here are synonymous with traditional long-lasting insecticidal nets, or LLINs) can still be effective at preventing malaria in regions with resistant vector populations [6]; however, as evidence of pyrethroid resistance mounts and documentation of the decreased ability of standard pyrethroid-only ITNs to control resistant mosquito populations increases, new classes of ITNs have been developed to perform against pyrethroid-resistant mosquitoes. These include pyrethroid-based ITNs that contain the insecticide synergist piperonyl butoxide (PBO, which inhibits mosquito monooxygenase enzymes that can detoxify pyrethroids), as well as newer dual active ingredient (dual-AI) ITNs that combine a pyrethroid AI with a second from a different class of insecticide—most notably either the pyrrole chlorfenapyr, an insecticide that disrupts adenosine triphosphate synthesis, or the insect growth regulator pyriproxyfen, which disrupts mosquito development and reproduction. ITNs refers to all bed nets treated with an insecticide and/or an insecticide synergist. The WHO defines long-lasting insecticidal nets as bed nets that have proven effectiveness after 20 washes and three years of use [7]. The dual active ingredient and piperonyl butoxide ITNs evaluated in this study have not demonstrated that they meet this standard.

Experimental hut and cluster randomized control trials suggest that these dual-AI ITN types provide greater mosquito control and superior protective efficacy against various epidemiological and entomological outcomes in areas with pyrethroid-resistant vectors [8]. For example, in Burkina Faso the distribution of ITNs with permethrin and pyriproxyfen (Olyset® Duo; Sumitomo Chemical Co., Ltd.) reduced clinical malaria incidence in children under 5 years old by 12% and infective mosquito bites by 51% compared to the standard pyrethroid-only ITNs [9]. In Tanzania, compared to standard pyrethroid-only ITNs, ITNs with PBO plus permethrin (Olyset® Plus, Sumitomo Chemical Co., Ltd) provided 44% greater reduction in prevalence at 9 months and 33% greater reduction at 21 months [10]. ITNs with alpha-cypermethrin and chlorfenapyr have shown high efficacy at controlling pyrethroid-resistant mosquitoes in experimental hut studies [11–13], demonstrating potential to better control malaria across sub-Saharan Africa. ITNs with alpha-cypermethrin and the insect growth regulator pyriproxyfen were also found to have high efficacy in controlling pyrethroid-resistant mosquitoes through feeding inhibition, sterilization, and the induction of mortality during experimental hut studies [14].

Access to new dual-AI ITNs is challenged by limited efficacy data for policy recommendations, higher costs than standard pyrethroid-only ITNs, and lack of evidence on cost-effectiveness compared with standard pyrethroid-only ITNs. However, in Phase 1 and 2 testing where safety and entomological impacts are assessed, Interceptor G2® ITNs (IG2; BASF AG), which combine alpha-cypermethrin and chlorfenapyr, performed to the thresholds required of pyrethroid-only ITNs and had no known adverse effects, receiving conditional WHO prequalification in January 2018 [15]. Similarly, Royal Guard® (RG; Disease Control Technologies, LLC), which uses a combination of alpha-cypermethrin and pyriproxyfen, received WHO prequalification in March 2019 [16]. While IG2 and RG ITNs have been approved for conditional use, WHO Vector Control Advisory Group guidance states that further evidence around dual-AI ITNs, specifically demonstration of their incremental epidemiological impact and the durability of this impact, is needed before policy recommendations can be made for their preferential use against pyrethroid resistant mosquitos (Additional file 1: Table S1].

The New Nets Project (NNP), funded by The Global Fund to Fight AIDS, Tuberculosis and Malaria and Unitaid, aims to help expand the evidence base for rational use of IG2, RG, and other ITNs with novel insecticide formulations while expediating the distribution of these nets to communities. This study focuses on evaluating the pilot distributions of IG2 taking place in Burkina Faso, Mozambique, Nigeria, and Rwanda, and RG in Mozambique and Nigeria. In addition, durability monitoring data will be collected by either NNP partners or by the US President’s Malaria Initiative (PMI)–funded VectorLink Project, and costing data for each country will be collected by NNP partners.

## Study objectives

The overall aim of the study is to describe the effectiveness and cost-effectiveness of IG2, RG, and PBO ITNs in comparison to standard pyrethroid-only ITNs. Specific objectives are organized into five study components: (1) malaria epidemiological surveillance to evaluate the impact of dual-AI ITNson malaria burden, (2) entomological surveillance to evaluate the impact of dual-AI ITNs on key entomological outcomes (3) anthropological data to assess how transmission risk is influenced by human behaviours, (4) assessment of the chemical and physical durability of the new ITN types, and (5) evaluation of the cost and cost-effectiveness of dual-AI ITNs.The epidemiological objective is to evaluate the effectiveness of IG2, RG, and PBO ITN distributions, compared to standard pyrethroid-only ITN mass distributions, in reducing:Malaria prevalence measured during annual cross-sectional surveys in children 6 months to 5 years (Burkina Faso, Mozambique, and Nigeria) and all ages (Rwanda).Passive malaria case incidence rates measured using routine surveillance systems (DHIS2).The entomological objective is to compare post-ITN distribution trends in vector densities, human biting rates, and entomological inoculation rates using CDCLTs and HLCs and to establish baseline. In addition, entomological objective is to evaluate insecticide susceptibility patterns in the primary vector species populations.The anthropological objective is to assess how human behaviour influences exposure risk and understand the key drivers of ITN use and non-use behaviour across districts with different types of ITN types.The ITN durability monitoring objective is to assess the attrition, survivorship, physical integrity, and insecticidal bioefficacy of all ITN types at baseline, 12 months, and 24 months.The cost-effectiveness objective is to combine data on product effectiveness (based upon case incidence rates measured for objective 1) and data on product prices and costs of delivery and deployment to estimate a mean cost per case averted for each ITN type.

## Methods

### Study sites

The study is composed of five distinct evaluations across four countries, one each in Burkina Faso, Nigeria, and Rwanda and two in Mozambique (Table 1). In each evaluation setting, these observational pilot studies accompany the national malaria control programme (NMCP)-led mass distribution campaigns of 2019 and 2020.

**Table 1 Tab1:** Study districts, type of insecticide-treated bed nets distributed through the mass campaign, and the pre-study baseline prevalence

Country	Study area	ITN AI	ITN brand	Under 5 baseline prevalence* (%)	Primary vector species	Pyrethroid resistance status (WHO tube test mortality)
Burkina Faso [17]	Banfora	Chlorfenapyr + alpha-cypermethrin	Interceptor G2	RDT: 13.8	*An. gambiae*	High (< 50%)
	Gaoua^†^	Standard pyrethroid-only	DuraNet LN, Interceptor, MAGNet, PermaNet 2.0	RDT: 32.4	*An. gambiae*	High (< 50%)
	Orodara	PBO	PermaNet 3.0	RDT: 13.6	*An. gambiae*	High (< 50%)
Northern Mozambique [18]	Mandimba	Pyriproxyfen + alpha-cypermethrin	Royal Guard	RDT: 48.6	*An. funestus*	Moderate (85–100%)
	Cuamba	Chlorfenapyr + alpha-cypermethrin	Interceptor G2	RDT: 48.6	*An. funestus*	Moderate (85–100%)
	Gurue^†^	Standard pyrethroid-only	DuraNet LN	RDT: 44.3	*An. funestus*	Moderate (85–100%)
Western Mozambique [18]	Changara	PBO	Olyset Plus	RDT: 29.4	*An. gambiae*	High (60–85%)
	Guro	Chlorfenapyr + alpha-cypermethrin	Interceptor G2	RDT: 47.6	*An. gambiae*	High (60–85%)
	Chemba^†^	Standard pyrethroid-only	DuraNet LN	RDT: 29.4	*An. gambiae*	High (60–85%)
Nigeria [19]	Asa	Chlorfenapyr + alpha-cypermethrin	Interceptor G2	RDT: 43.7	*An. gambiae*	Variable (12–94%)
	Moro	Pyriproxyfen + alpha-cypermethrin	Royal Guard	RDT: 43.7	*An. gambiae*	Variable (12–94%)
	Ejigbo^†^	Standard pyrethroid-only	DuraNet LN	RDT: 54.9	*An. gambiae*	Variable (12–94%)
	Ife North	Alpha-cypermethrin + PBO	Veeralin	RDT: 54.9%	*An. gambiae*	Variable (12–94%)
Rwanda [20]	Karongi	Chlorfenapyr + alpha-cypermethrin	Interceptor G2	RDT: 3.1 Microscopy: 1.8	*An. funestus*	Low (85–100%)
	Nyamagabe^†^	Deltamethrin	Yahe LN	RDT: 14.4 Microscopy: 8.7	*An. funestus*	Low (85–100%)
	Ruhango	Deltamethrin (and IRS)	Yahe LN	RDT: 14.4 Microscopy: 8.7	*An. funestus*	Low (85–100%)

*IG2* Interceptor G2, *IRS* indoor residual spraying, *ITN* insecticide-treated bed net, *PBO* piperonyl butoxide, *RDT* rapid diagnostic test, *RG* Royal Guard

*Prevalence surveys were not conducted at the study area level. Details on each survey methodology can be found in the referenced document for each country. Additional details on each evaluation context are available in Additional file 2: Annex S1

^†^Indicates study control area

IG2s were deployed in five districts (Burkina Faso, Nigeria, western and northern Mozambique, Rwanda), RGs deployed in two districts (Northern Mozambique and Nigeria) and PBOs deployed in three districts (Burkina Faso, Western Mozambique, and Nigeria). In Rwanda, one district deployed IRS in combination with standard pyrethroid-only ITNs in comparison to pyrethroid-only ITNs alone (Figs. 1, 2, 3 and 4).

**Fig. 1 Fig1:**
[figure not shown]
Study districts in Burkina Faso

**Fig. 2 Fig2:**
[figure not shown]
Study districts in Mozambique

**Fig. 3 Fig3:**
[figure not shown]
Study districts in Nigeria

**Fig. 4 Fig4:**
[figure not shown]
Study districts in Rwanda

### Study design

The study is an opportunistic, quasi-experimental design with control groups; dual-AI ITNs (intervention) were distributed alongside standard pyrethroid-only ITNs (control) during multi-product universal coverage campaigns. As such, these are all observational studies that leverage the 2019 and 2020 ITN mass distribution campaigns and the district health information systems and existing vector surveillance programmes, which serve as monitoring platforms. Intervention districts received a dual-AI ITN type (IG2, RG, or PBO), while control districts received either standard pyrethroid-only ITNs or standard pyrethroid-only ITNs plus IRS. The ITN types are not always distinguishable by size, shape, or colour, but are identifiable by their sewn-in product labels.

### Identification of intervention and control study districts

Decisions on what brand/type of ITN to procure, and where to distribute them were made by each respective NMCP through consultation with partner institutions and international donors. The NMCPs used the dual-AI ITNs in their mass campaigns with the stipulation that there be an accompanying pilot evaluation based on their distribution and the study designs took advantage of natural comparisons among districts that results from these decisions. The NMCPs of Burkina Faso (2019) and Rwanda (2020) incorporated IG2 ITNs into their mass distribution campaigns. Mozambique and Nigeria both incorporated IG2 and RG ITNs into their 2020 mass campaigns. In addition, Burkina Faso (2019), Mozambique (2020), and Nigeria (2020) incorporated PBO ITNs into their mass campaigns. All districts included in the mass distribution campaigns receive a single type of net. A subset of districts that receive IG2, RG, PBO, and pyrethroid-only ITNs were selected by the partners as study districts (Table 2).

**Table 2 Tab2:** ITN distribution by country National Malaria Control Programmes

Geography	Study period	ITNs evaluated	ITN distribution completed
Burkina Faso	2019–2022	IG2, PBO	June 2019 (PBO) August 2019 (standard) October 2019 (IG2)
Northern Mozambique	2020–2022	IG2, RG	November 2020
Western Mozambique	2020–2022	IG2, PBO	December 2020
Rwanda	2020–2022	IG2	February 2020 (standard) May 2020 (IG2)
Nigeria	2020–2022	IG2, RG, PBO	November 2020

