### Epidemiological component

Across all countries, malaria burden is measured through cross-sectional surveys, routine health facility data, and in most evaluations, antenatal care surveillance. For all countries, the study aims to conduct all surveys during high transmission seasons. This is complicated in many areas because of seasonal rains that impact operations. In addition, because of the timing of the grant and the net distribution, with the necessity to conduct a baseline survey before or contiguous with distribution, the timing of baseline surveys were adjusted in Rwanda, Nigeria, and Mozambique. Efforts are made to ensure that the post distribution cross-sectional survey timing is within a higher transmission season and is consistent across the years for comparison. In Burkina Faso, where four rounds of SMC are done annually in children 3 months to 5 years during the malaria transmission season, the study aims to time the surveys before SMC campaigns to ensure that the measurements are not conflated with the effects of the first round of seasonal malaria chemoprevention.

In each study district, villages were randomly selected for participation using probability proportionate to size, from which households were sampled either randomly or following a standard systematic sampling approach (e.g., every third household) During each survey a new set of households with eligible participants are selected (Table 3).

**Table 3 Tab3:** Cross-sectional survey methodology by country

Country	Participants		Sample size (households)	Survey months
	Questionnaire	Prevalence		
Burkina Faso	Household head or primary caregiver	Child aged 6 to 59 months	570 per year (2280 total)	• July 2019 • July 2020 • July 2021 • July 2022
Northern and western Mozambique	Household head or primary caregiver	Child aged 6 to 59 months	2520 per year (7,560 total)	• September–October 2020 • September–October 2021 • August–September 2022
Nigeria	Household head or primary caregiver	Child aged 6 to 59 months	1680 per year (5,040 total)	• September 2020 • November 2020 • November 2021
Rwanda	Household head or primary caregiver	All household residents aged 6 months and older	450 per year (1,800 total)	• February 2020 • December 2020 • November 2021 • November 2022

*LGA* local government area

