#### Epidemiological surveillance analysis

The trials are planned under a superiority, difference-in-differences (DiD) framework. The comparisons will consist of one-sided tests of the null hypothesis that the outcomes (reductions in parasite prevalence or case incidence rate from baseline to end line) in each intervention district are statistically the same as the outcomes in the appropriate control district control arm.

Malaria infection prevalence, determined by RDT tests during the cross-sectional surveys, will be analysed by an appropriate difference-in-differences model comparing changes in prevalence from year to year across study districts (intervention type). Considering sample size constraints, a single indicator age group will be targeted using a clustered sampling approach, clustering observations at a sub-district level (either by sector, health facility catchment, or village—whichever is most practical). Statistical analysis is done using Stata (version 14.2 or later). A difference-in-differences approach will assess matched-pair comparisons of the mean change in malaria prevalence from year to year, before and after ITN distribution across each study districts (intervention/control) comparison. The approach taken within each evaluation setting is powered independently to compare changes in prevalence observed in the ITN intervention districts to changes in the prevalence observed in the appropriate ITN control district. However, given the proposed study design and sampling frame, secondary post-hoc analyses, with Bonferroni’s correction for multiple comparisons, will likely be able to detect an effect size difference of around 20% between any two ITN types at 24 months. The protective efficacy of dual-AI ITNs is determined by multilevel logistic regression model for each year, adjusted for age and individual ITN use the previous night, with clustering at the district level.

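### Burkina Faso: the first survey follows PBO net distribution in Orodara, so the PBO survey difference-in-differences has no clean pre-distribution measurement

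*Protocol article*

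**What the plan says.** All references are to the protocol article.

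- **Distribution dates.** Table 2, in the column headed "ITN distribution completed", gives for Burkina Faso "June 2019 (PBO) August 2019 (standard) October 2019 (IG2". By Table 1, PBO is Orodara, standard is Gaoua (the control) and IG2 is Banfora.
- **Survey dates.** Table 3 lists the Burkina Faso rounds as "July 2019 • July 2020 • July 2021 • July 2022", with a sample of "570 per year (2280 total" households.
- **Baseline rule.** The Epidemiological component section explains the survey timing by the grant and campaign schedule: "with the necessity to conduct a baseline survey before or contiguous with distribution, the timing of baseline surveys were adjusted in Rwanda, Nigeria, and Mozambique". Burkina Faso is not in that list.
- **Analysis.** The Epidemiological surveillance analysis section defines the outcomes as "reductions in parasite prevalence or case incidence rate from baseline to end line" and the prevalence comparison as the mean change "before and after ITN distribution across each study districts (intervention/control) comparison".
- **Status of the outcome.** The Epidemiological power section makes district-level survey prevalence the outcome on which the evaluations are powered. For Burkina Faso it plans on a 30% relative reduction with the new nets and 5% with standard nets, tested one-sided at 0.0125 with 80% power.
- **Routine data.** Their analysis starts about one year before the campaigns.

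**The concern.** A difference-in-differences needs a first measurement taken before either district is exposed, or at least with both at the same stage. Here the two districts in the PBO contrast are at different stages in July 2019. Orodara's campaign is finished and Gaoua's is not. Whatever the PBO nets had already done by then is built into Orodara's starting value and is lost from its measured change, while the control district keeps more of its own change.

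At stake is the conclusion on PBO nets in Burkina Faso. The Discussion presents the pilots as including a formal evaluation of PBO nets in West African settings with intense resistance. With a one-sided superiority test, an attenuated estimate could be read as no incremental PBO benefit when part of the benefit fell before the first survey.

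**Working it through.** **1. Is July 2019 the first round?** 570 × 4 = 2280, which reproduces the total in Table 3. There are four rounds and none before July 2019. Table 3 does not label that round as baseline, but no other survey could be. The prevalences in Table 1 cannot stand in, because its footnote says those surveys were not done at study-area level.

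**2. Order of events in 2019.**

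| Month | Event |
|---|---|
| June | PBO distribution completed (Orodara) |
| July | First survey, all three districts |
| August | Standard distribution completed (Gaoua) |
| October | IG2 distribution completed (Banfora) |

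Only Orodara has its first survey after completion.

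**3. Effect on the measured PBO reduction.** Let f be the share of the planned 30% reduction already present in Orodara in July 2019. The documents do not give f, so the values below are assumptions. The July 2019 value is (1 − 0.30f) times the true starting prevalence and the follow-up value is 0.70 times it, so

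measured PBO reduction = 1 − 0.70 / (1 − 0.30f).

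Against the planned 5% control reduction, the ratio of the two districts' changes is [0.70 / (1 − 0.30f)] / 0.95.

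| f | Measured PBO reduction | Ratio PBO / control |
|---|---|---|
| 0 | 1 − 0.70/1.000 = 30.0% | 0.737 |
| 0.10 | 1 − 0.70/0.970 = 27.8% | 0.760 |
| 0.25 | 1 − 0.70/0.925 = 24.3% | 0.797 |
| 0.50 | 1 − 0.70/0.850 = 17.6% | 0.867 |

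**4. What this would do to power.** Suppose the design has exactly 80% power for the planned difference of 30% − 5% = 25 points at one-sided 0.0125, and the standard error is unchanged. With z-values 2.241 and 0.842, power is Φ(3.083 × d/0.25 − 2.241), where d is the measured PBO reduction minus 0.05. For f = 0, 0.10, 0.25 and 0.50, d is 0.250, 0.228, 0.193 and 0.126, and power is about 80%, 72%, 56% and 25%.

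**5. Direction if control nets were also partly out.** Table 2 gives completion months only, so some Gaoua households may have had new nets in July. If a share g of the control's 5% was also present, the ratio becomes 0.737 × (1 − 0.05g)/(1 − 0.30f). It exceeds 0.737, that is, it moves toward no effect, whenever 0.30f > 0.05g, or f > g/6. With PBO distribution complete and control distribution not, that is the likely case, but the documents do not prove it.

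**The case against.** Several counter-arguments have force.

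- **The baseline rule allows a survey contiguous with distribution.** June and July are adjacent months, so the timing may be tolerated by that wording. It still does not fit a before-and-after contrast in which one district's campaign is complete and the other's is not.
- **The limitation is disclosed.** The Discussion admits short pre-intervention periods and campaign timing that differed across districts. It also names duration of net ownership and baseline differences as matters for the local analyses. This partly covers the unequal follow-up (July 2020 is about 13, 11 and 9 months after PBO, standard and IG2 completion). It does not say that Orodara's first survey follows its nets, and gives no rule for handling that.
- **The bias may be small.** This stands. The lag from completion is about one month, and nothing in the article supports a large f.

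A reader might also infer more than the article supports:

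- *That the PBO evaluation has no baseline at all.* Only the survey contrast is affected. The incidence analysis, which also feeds the cost-effectiveness work, has about a year of earlier data. The yearly multilevel models of protective efficacy are not described as relying on July 2019 either.
- *That the estimate could turn against PBO.* On the planning figures the ratio reaches 1 only when 1 − 0.30f = 0.70/0.95 = 0.737, that is f ≈ 0.88. That would require nearly the whole two-year average effect about a month after completion.
- *That control households still had only old nets in July.* Completion months do not show this.
- *That Rwanda has the same fault.* Its control distribution was completed in the baseline survey month, but the order within the month is not given and the article names Rwanda as adjusted. An early control effect there would favour IG2, the opposite direction.

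**Conclusion.** The point holds for one contrast: PBO versus standard nets on survey prevalence in Burkina Faso. The dates are certain and the tables conflict with the analysis as described. The direction is toward no effect if PBO nets lowered prevalence at all by July 2019 and this was not offset by early control nets (f > g/6). The size cannot be derived from the documents. Under assumed shares of 10%, 25% and 50%, a true 30% reduction would be measured as about 28%, 24% and 18%, and at about one month after completion the lower end may well apply. The routine-incidence contrast does not share the problem, provided the switch date is each district's own.

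**What to change.** 1. State in the analysis plan that Orodara's July 2019 survey follows distribution, and do not treat it as a pre-intervention point.
2. Use the ITN questions already in the household questionnaire to report the share of households in Orodara and Gaoua that held campaign nets at that round. Run a sensitivity analysis of the PBO contrast on it, for example over a stated range of f and g.
3. Report the PBO survey difference-in-differences as likely biased toward no effect, so that a null is not read as absence of PBO benefit.
4. Interpret it beside the planned routine-incidence difference-in-differences, with district-specific distribution dates.

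This needs no new data collection. The cost is that the Burkina Faso PBO survey comparison supports a weaker conclusion. Replacing it outright with routine incidence is not required: survey prevalence is the powered outcome, and the Discussion itself describes routine data as often limited by poor integrity and supply shortages. Neither source should carry the PBO conclusion alone.
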